### Engagement and Usage Measures

The digital systems will collect anonymized descriptive data relating to engagement and usage of the service users with the platforms. Data collected will include the number of sessions attended, time spent in the platform, number of activities completed, number of minutes per log-in, number of resources accessed. A session is defined as an instance where a user logs on to the system. Session time will be always an imperfect calculation, as users may take breaks within a session, without formally log out of the system. To prevent this overestimation, periods of more than 30 min without interaction will be taken as 1 min and periods of inactivity longer than 3 h will start the count on a new session. Use of different program components will be measured.

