
### Phase 1

Weeks 1–6 will consist of 3 exercise sessions per week. Session 1 will be an online live streamed activity conducted by 2 Nuffield Health trained rehabilitation specialists. One practitioner will run the exercise session and the second will answer questions via the online chat function. The stream will be a 1-way stream, meaning that whilst multiple patients will access the stream at any given time, they will not be recorded/filmed nor will their personal details be visible to the group. A maximum of 10 patients will join a stream at any time. The live stream will last up to 45-min followed by a 15-min period for questions via the secure online chat function or alternatively spoken questions can be provided should the patient have microphone functionality.

The second session of the week during phase 1 will be self-directed. The patient will be directed to a pre-recorded guided exercise session located on a dedicated online platform (Vimeo, New York, USA). This will be a 45-min activity which the patient completes at their leisure. All exercises are designed such that they can be carried out with ease at home.

The third exercise session of the week is described as “build your own.” The patient's workbook provides the patient a menu of activities suitable for them, which they may select to populate an exercise session commensurate with their personal threshold.

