Following successful completion of phase 1, patients will progress to the phase 2 face to face programme. This phase will be conducted in strictly controlled gym environments conforming to all necessary Government and Public Health England (PHE) guidance. As per phase 1, phase 2 will consist of 3 exercise sessions per week. The first session of the week will be a rehabilitation specialist lead group exercise programme. In appropriately prepared and ventilated spaces, groups of up to 5–10 patients will engage in a 45-min exercise class followed by 15 min for questions and answers. Exercises will consist of aerobic and strength-based exercises as well as stability and mobility. In order to promote continued self-management, the second exercise session of the week will be a remote pre-recorded session that the patient will carry out at home independently, as per phase 1. Similarly, the third session of the week, “build your own” will remain; however, the patient will be encouraged to complete this session within a supervised gym environment. The rehabilitation specialist will be on hand within pre-defined time slots to provide advice and guidance. The patient will again receive a weekly consultation with the rehabilitation specialist following the aforementioned themes. This will culminate between weeks 12 and 13 with a final assessment, summary report and sign-posting to additional services where required.

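### The 30-minute inactivity cut-off is shorter than the 45-minute exercise videos and streams, so a completed session can be logged as 1 minute in the two time-based usage metrics

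*Protocol article*

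**What the plan says.** The section Engagement and Usage Measures lists five usage metrics: "number of sessions attended, time spent in the platform, number of activities completed, number of minutes per log-in, number of resources accessed". It adds that use of the different programme components will be measured. It defines the unit of counting: "A session is defined as an instance where a user logs on to the system". It accepts that session time is imperfect because "users may take breaks within a session, without formally log out of the system", and guards against the resulting overestimate with two rules. The first is that "periods of more than 30 min without interaction will be taken as 1 min". The second is that "periods of inactivity longer than 3 h will start the count on a new session". The article does not define interaction and makes no exception for video playback.

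The content to which these rules might apply is described under Phase 1 and Phase 2. Each week of Phase 1 has a live session of up to 45 minutes ("The stream will be a 1-way stream"), followed by 15 minutes for questions by chat or microphone. It also has a recorded guided session: "This will be a 45-min activity which the patient completes at their leisure". In Phase 2 the live session becomes a face-to-face class, but the recording continues: "the second exercise session of the week will be a remote pre-recorded session that the patient will carry out at home independently". The third weekly session is chosen by the patient from a menu in the workbook and is neither a stream nor a video.

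**The concern.** An idle-time rule of this kind suits content that the user clicks through, where half an hour without a click probably means the user has left. Here the main digital content is exercise done in front of a screen. A gap of more than 30 minutes without contact is what one would expect from a patient who follows the whole session. Because the cut-off is shorter than the content, the rule treats that patient as absent.

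The time metrics would then reflect how often a patient touches the device rather than how long the patient exercises. Two patients with identical adherence could differ widely in recorded minutes, and a patient who finishes a video could not be told apart from one who opened it and walked away.

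The word session adds to the difficulty. Under Phases 1 and 2 it means an exercise session, while in the usage section it means a log-on. The count of sessions attended therefore cannot by itself separate a completed workout from a brief log-in. The article links the benefit of digital rehabilitation to strong adherence and says that the digital component will be evaluated (New Models of Rehabilitation), so usage data that misdescribe adherence would weaken that part of the report.

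**Working it through.** The article gives no expected engagement figure to reproduce, so the check applies the stated rule to the stated schedule.

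**Inputs from the article**
- A gap of more than 30 minutes is credited as 1 minute (Engagement and Usage Measures).
- The new-session threshold is 3 hours, which a 45-minute item does not reach (same section).
- Phase 1, 6 weeks: one live stream of up to 45 minutes plus 15 minutes of questions, and one 45-minute recording, each week.
- Phase 2, 6 weeks: one recording each week, taken at the same 45 minutes.

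**Assumptions not in the article**
- The streams and recordings are logged under this rule.
- Playback alone is not interaction.
- Streams run the full 45 minutes.
- The frequency of screen contact is unknown, so it is varied below.

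**Rule.** credited(gap) = 1 if gap > 30 minutes, otherwise credited(gap) = gap.

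**One item.** A 30-minute gap is credited 30 and a 31-minute gap is credited 1. An untouched 45-minute session is credited 1, and 1/45 = 2.2%. A patient who opens the same video and leaves for 45 minutes is also credited 1. One touch halfway gives two gaps of 22.5 minutes, credited 22.5 + 22.5 = 45. The timing of the touch matters: a single touch at minute 10 leaves a 35-minute gap, so the credit is 10 + 1 = 11.

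**Scheduled stream and video time.** Phase 1: 6 × (45 + 45) = 540 minutes. Phase 2: 6 × 45 = 270 minutes. Total: 810 minutes over 12 + 6 = 18 items.

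| Scenario | Credited (min) | Actual (min) | Share |
|---|---|---|---|
| Phase 1, no screen contact | 12 × 1 = 12 | 540 | 2.2% |
| Phase 1, active chat for 15 min after each stream | 12 + 6 × 15 = 102 | 540 + 90 = 630 | 16.2% |
| Phase 1, one touch mid-stream plus chat, video untouched | 6 × 45 + 6 × 15 + 6 × 1 = 366 | 630 | 58.1% |
| Phase 1, one touch midway through every item | 12 × 45 = 540 | 540 | 100% |
| Phase 2 recordings, no screen contact | 6 × 1 = 6 | 270 | 2.2% |
| 12 weeks, no screen contact | 18 × 1 = 18 | 810 | 2.2% |
| 12 weeks, one touch midway through every item | 18 × 45 = 810 | 810 | 100% |

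The recordings are the clearest case, because they have a fixed length, are done alone and have no described chat. Over 12 weeks they amount to 12 × 45 = 540 minutes, credited as 12 if untouched. Every row except the Phase 2 one describes a patient who completed all the streams and videos in the period shown; the Phase 2 row does so for its recordings. The spread therefore comes from screen contact alone.

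**What does not move.** The counts of log-ons, activities completed and resources accessed do not depend on minutes and are the same in every scenario.

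**The case against.** The strongest reply is that little depends on these minutes. The usage data are described as anonymised and descriptive. Three of the five listed metrics are counts that the rule leaves alone, use of programme components is measured as well, and Statistical Analysis separately provides for monitoring participation and recording reasons for non-compliance. This stands, and it limits the point to two metrics.

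A reader might go further and infer that full adherence will be recorded as almost none, or that a dose-response conclusion could be reversed. The article does not support either reading. Activities completed and resources accessed would still show adherence. No section ranks minutes as the main engagement measure or names them as a dose, an exposure or an adherence definition. The mediators and moderators promised in the Abstract and Discussion are not tied to any usage variable.

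It is also fair to say that 2.2% is an extreme. A second practitioner answers questions by chat during the live stream, streams last at most 45 minutes (one of 30 minutes or less never triggers the rule), and one well-timed touch restores full credit. Interaction is undefined, and a fuller document could count playback. Nor does the article say which systems are logged. The recordings sit on a dedicated video platform, and other audio-visual contact runs on a system separate from the main application. If those are outside the logging, the rule never reaches this content, and the time metrics simply omit it.

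What remains is a rule stated in the article, without exception, whose cut-off is shorter than the content it would most naturally be applied to.

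**Conclusion.** The point holds in a limited form. Applied as written to tracked content, and if playback is not interaction, the rule credits a completed, untouched 45-minute session as 1 minute and cannot distinguish it from an abandoned one. For a patient who completes every scheduled stream and video, recorded time could be anything from 18 to 810 of 810 minutes, depending only on screen contact. That makes time spent in the platform and minutes per log-in unreliable as measures of exercise done.

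The consequence is confined to descriptive engagement reporting and to any later analysis that chooses to use minutes. No primary or secondary outcome is touched, and neither is any analysis the article specifies. The change is worth making because the rule gives a wrong result for the programme's own content and is cheap to correct.

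**What to change.** - State which platforms are logged, and define interaction so that video playback or live-stream attendance counts as activity up to the length of the content. A simpler alternative is a cut-off above 45 minutes.
- Apply the idle rule only to other pages.
- Report log-ins and exercise sessions completed as separate variables. Base adherence on exercise sessions or activities completed, not on log-ins or minutes.

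The cost is a change of definition and some extra log processing, provided that the platforms supply playback and attendance records, which the article does not state. Playback credit may slightly overcount patients who leave a video running. A higher cut-off has the same weakness, since it would also credit longer genuine breaks.

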### Statistical Analysis

Participation levels will be monitored throughout the programme and reasons for withdrawal or non-compliance will be recorded. All participants are selected according to clinical criteria alone with no other factors influencing participation so as to limit selection bias. Information biases are limited via the prospective nature of this evaluation and the methodology employed to collect mandatory data at each designated time point. As well as the primary and secondary outcome measures being collected, a detailed clinical history and additional triage will be undertaken for each participant. This will limit confusion bias through the identification of relevant confounding clinical variables. Efficacy of treatments over time will be measured using mixed effects models. To complement the *post-hoc* comparisons, the magnitude of change on the primary and secondary outcomes measures will be established using Cohen's *d* statistic. Bonferroni corrected *p*-values will be reported for multiple comparisons. Participants with missing data will be removed for analysis with complete-case analysis being utilised.

An interim-analysis will be performed on the primary endpoint when 50% of participants have completed up to the 6-month follow up point. The interim analysis will be performed by an independent statistician. The statistician will report to the principal investigator ([name]) only. The principal investigator will have unblinded access to all data and will discuss the results of the interim analysis with the project team.

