## Methods and Analysis

### Trial Design

The protocol presented herein reflects Protocol Number 01. Any amends to this protocol will be detailed in full within the ISRCTN registry. This observational cohort study will be conducted following the STROBE statement (25) for observational studies with the protocol reported in line with SPIRIT Statement (26). We will examine the effectiveness of a 12-week blended community rehabilitation programme on improvements in HR-QoL and reductions in symptoms of COVID-19, in individuals recovering from the disease.

This evaluation will be conducted in concert with the NHS. Initially the programme will be deployed across 4 NHS locations, namely; University Hospitals of North Midlands Trust, Newcastle upon Tyne Hospitals NHS Foundation Trust; Birmingham and Solihull Community Care Group and Central Manchester University Hospitals Trust. Whilst these locations are clustered in the North and Midlands they are demographically and economically diverse. The NHS sites will be serviced by 8 surrounding Nuffield Health Fitness and Well-being Centres, all of which are registered with the Care Quality Commission and are located within a 20-mile radius of a participating NHS site. Each trust will be assigned 2 rehabilitation specialists from Nuffield Health to support the programme. As this intervention will be offered as a National service, recruitment is open ended beginning in September 2020. Nuffield Health intend to expand provision by operationalising all 112 of its fitness and well-being centres in 2021. These locations cover all 7 geographical regions as defined by NHS criteria. An initial evaluation cohort will not exceed 160 participants ensuring that a participant practitioner ratio of 1:10 is not exceeded.

Those wishing to access the programme can do so via NHS referral, this can be through doctor, nurse or other allied health professional such as a physiotherapist. Patients will only be referred if they meet the qualifying criteria presented in Table 1.

**Table 1 T1:** Inclusion and exclusion criteria.

**Inclusion criteria**	**Exclusion criteria**
Previous diagnosis of COVID-19	Active COVID-19 symptoms
Able to walk independently for a minimum of 20 m	Are already receiving community rehabilitation
Must have access to the internet and smartphone/tablet/personal computer (with adequate technological literacy)	Have un-managed medical conditions that contraindicate unsupervised exercise

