## Measures

Outcome data will be collected at 0, 6, and 12 weeks and again at 6- and 12-months post-intervention. Self-report data will be collected via digital application (MyWellbeing, Nuffield Health, London, UK). The patient will be emailed and provided a push-notification prompting them to complete the aforementioned questionnaires. Whilst this evaluation will not utilise any formal comparison group, it is intended that collaboration with trusts will support the analysis of anonymised “usual care” outcome data. This is likely to come from community physiotherapy and/or modified pulmonary rehabilitation.

All data will be securely stored on a dedicated Nuffield Health server and will be retained in line with the organisations publicly available data retention schedule. Modifications to data written to the database will be documented through via an internal inquiry system. Data entered into the database will be retrievable for viewing throughout by those granted secure access privileges associated with an identification code and password. Any data errors will be summarised along with detailed descriptions for each specific problem in a data query reports, which will be sent to the study Outcomes Analyst. The Outcomes Analyst will check any inconsistency, checking other sources to determine required corrections. Any coding changes required within the digital data capture system will then be implemented within 24 h.

Complete back up of the primary database will be performed twice a month. Incremental data back-ups will be performed on a daily basis. In addition to system back-ups, additional measures will be taken to back-up and export the database on a regular basis at site level. The outcomes analyst will send weekly email reports with information on missing data, missing forms, and missing visits to site level co-ordinators who will then rectify immediately as and when required. Data security audits will be completed by the Nuffield Health Information Security group on a quarterly basis. Full details of group membership and details of audit processes can be provided upon request.

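### The plan names mixed effects models but removes participants with missing data; this discards observed assessments and biases the before-after change whenever completion is related to outcome

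*Protocol article*

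**What the plan says.** Two sentences in one paragraph of the protocol article (Statistical Analysis) bear on this. On the model: "Efficacy of treatments over time will be measured using mixed effects models". On missing data: "Participants with missing data will be removed for analysis with complete-case analysis being utilised". The second is a stated rule, so this is not detail left to a later plan.

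The Measures section sets the schedule: "Outcome data will be collected at 0, 6, and 12 weeks and again at 6- and 12-months post-intervention". That is one baseline and four follow-ups. Self-report outcomes come through an app: "The patient will be emailed and provided a push-notification prompting them to complete the aforementioned questionnaires". The same section says: "Whilst this evaluation will not utilise any formal comparison group". Trial Design caps the first cohort: "An initial evaluation cohort will not exceed 160 participants ensuring that a participant practitioner ratio of 1:10 is not exceeded".

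The article describes data at each time point as mandatory, records reasons for withdrawal, and has weekly missing-data reports sent to sites. It gives no expected rate of missing data and no sensitivity analysis for it.

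**The concern.** A mixed model fitted by likelihood uses every recorded assessment and gives valid estimates when missingness depends only on observed data. That is a main reason for choosing it for repeated measures. Removing incomplete participants first gives up this property. Someone with data at 0, 6 and 12 weeks who misses month 12 would drop out of the 6- and 12-week results as well.

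Two things are at stake for both primary outcomes. Precision is lost. The estimated change also becomes the change among people who completed every assessment, which differs from the cohort's change whenever completing is related to how a person fared. In a two-arm trial some of that error might cancel between arms. Here the estimate is a single-group before-after change, so all of it stays.

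**Working it through.** The article gives no power, effect size, standard deviation or dropout rate, so it has no figure to reproduce. The rates and parameters below are assumptions.

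**1. How many participants survive the literal rule**

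Inputs: cohort cap 160 (Trial Design); four follow-ups (Measures); per-follow-up miss probability p, assumed. Baseline is taken as complete.

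If misses are independent, complete cases = 160 × (1 − p)^4. If the same people miss every time, complete cases = 160 × (1 − p).

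| p | independent misses | same people miss each time |
|---|---|---|
| 5% | 160 × 0.815 = 130 | 152 |
| 10% | 160 × 0.656 = 105 | 144 |
| 15% | 160 × 0.522 = 84 | 136 |
| 20% | 160 × 0.410 = 66 | 128 |

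Relative to a fully observed cohort, the standard error grows by √(160/130) = 1.11 to √(160/66) = 1.56 in the independent case.

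**2. What the rule does to the estimate**

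Simulation assumptions: 160 participants, five visits, standardised outcome scored so that higher is better, correlation 0.6 between visits, the same true change at all four follow-ups, monotone dropout, 400 replicates. Where dropout depends on outcome, its log-odds rise by 1.5 per SD of worse change. Complete cases are compared with a likelihood fit to all observed data (unstructured mean and covariance). Entries are the estimated change in SD at 12 weeks / 12 months.

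| Dropout depends on | True change | Incomplete | Complete cases | All observed data |
|---|---|---|---|---|
| nothing | 0.30 | 40% | 0.30 / 0.30 | 0.30 / 0.30 |
| change already observed (MAR) | 0 | 20% | 0.12 / 0.09 | 0.00 / 0.00 |
| change already observed (MAR) | 0 | 40% | 0.24 / 0.18 | 0.00 / 0.00 |
| change already observed (MAR) | 0.30 | 20% | 0.43 / 0.39 | 0.30 / 0.30 |
| change already observed (MAR) | 0.30 | 40% | 0.55 / 0.48 | 0.30 / 0.30 |
| current, unobserved change (MNAR) | 0 | 20% | 0.14 / 0.14 | 0.04 / 0.03 |
| current, unobserved change (MNAR) | 0 | 40% | 0.28 / 0.27 | 0.07 / 0.05 |

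With no true change and MAR dropout of non-improvers, a nominal 5% test on completers at 12 months rejects 20% of the time (20% incomplete) or 52% (40% incomplete).

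**3. The sign can reverse**

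In this set-up dropout depends on each person's deviation from the mean change and the distribution is symmetric. If improvers stop responding instead, the bias keeps its size and changes sign. For a true change of 0.30 at 12 weeks under MAR:
- 20% incomplete: 0.30 − (0.43 − 0.30) = 0.17
- 40% incomplete: 0.30 − (0.55 − 0.30) = 0.05

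**4. How much depends on the reading of the rule**

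A second set-up assumes a true change of 0.30 SD at 6 weeks and 0.50 SD from 12 weeks on, MAR dropout of non-improvers (log-odds 0.5 to 1.0 per SD) and 55% complete at all five visits. Requiring all five visits gives a 12-week change of 0.60 to 0.68 SD. Requiring only 0, 6 and 12 weeks gives about 0.53 to 0.56 SD. Most of the excess at 12 weeks comes from the five-visit reading.

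**The case against.** **The direction is not established.** A reader might infer that the rule favours the programme, because people who feel no benefit are the ones who stop. Nothing in the article supports that over the alternative that recovered patients ignore app prompts. This objection stands: the sign is unknown.

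**The literal reading may be too harsh.** The article does not say that completeness means all five visits. Its interim analysis is triggered when half the participants reach 6 months, and requiring 12-month data there would exclude people not yet due, so completeness must be specific to the analysis in that case at least. This stands in part. A narrower reading shrinks the bias without removing it, and the sentence does speak of participants rather than visits.

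**Independent misses overstate the loss.** Non-response usually clusters within people. This stands, and the last column of the first table shows the other extreme.

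**Complete-case change does not strictly need data missing completely at random.** A reader might infer that it does. It is enough that completing is unrelated to change, or that it depends only on covariates in the model. This stands, but the article makes no such argument.

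**The article already limits missing data.** Mandatory fields, weekly reports and retention measures may keep it low. They do not alter how missing data are analysed, and the article itself provides for recording withdrawals.

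**The fix does not separate programme effect from natural recovery.** That is true of any uncontrolled cohort, and it is no reason to add a second, avoidable source of bias.

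**Conclusion.** The rule is wrong as written. Followed literally, it throws away recorded primary-outcome data and undoes the main advantage of the chosen model. The before-after change is then biased whenever completion is related to outcome, with no comparison group to absorb the bias.

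The precision loss depends on an assumed miss rate. At 20% per follow-up, from 66 (independent misses) to 128 (the same people each time) of 160 remain. The bias is zero if completion is unrelated to change, positive if non-improvers leave and negative if recovered patients leave. The simulated values show that it can be large enough to matter, and they do not estimate what will happen in this cohort. A fixed percentage inflation, or a claim that the programme will necessarily look better than it is, would go beyond the article.

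A likelihood-based mixed model on all observed data removes the bias under MAR only. In the MNAR run with no true change and 40% incomplete, it left 0.07 SD at 12 weeks against 0.28 SD for completers.

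**What to change.** Replace the missing-data sentence in Statistical Analysis with:

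> All participants with at least one outcome assessment are included; the mixed model is fitted by (restricted) maximum likelihood to all observed assessments, with time as a categorical factor. Complete-case results are reported as a sensitivity analysis, with a delta-adjusted analysis for departures from missing at random.

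The delta-adjusted analysis should shift unobserved outcomes in both directions, because the sign of any selection is unknown. The covariance structure and imputation for QALYs can be left to the statistical analysis plan.

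The cost is a change of wording and one extra sensitivity analysis. No new data are needed, and the schedule and instruments do not change.
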